## Discussion

The proposed project will discuss the feasibility and efficacy of the JRS WAVE. Uptake from screening to recruitment, adherence to the intervention and rates of dropout will be discussed. Feedback from clinicians in terms of system utility will be explored. Feedback from clients on the perceived benefits of this type of rehabilitation and enjoyment and ease of use of the games will also be discussed. Changes in pain and fatigue within each session and between the intervention and control groups will be analysed. Differences in activity levels during the two different interventions (JRS WAVE versus group exercise) will be investigated. Between-group differences for outcome measures of upper-limb function as well as balance and mobility will be investigated.

The primary outcome of efficacy consists of the differences in activity levels from using video technology in rehabilitation compared with usual rehabilitation. It will also provide data for new controller- and device-free motion capture software on measures of upper-limb function, balance and mobility. Much of the published research reviewing the effectiveness of interactive technology games with commercial devices has not used motion capture software in a controller-free situation. For example, the wii™ system for balance requires standing on a platform and the upper-limb tasks require the client to hold (or have strapped to their hand if they do not have grasp capacity) a device that the sensor recognises [6].

This software has been iteratively designed with feedback from the clinicians to form a system that meets the needs of stroke clients in the acute hospital setting as they begin their rehabilitation pathway. This system is vastly configurable, giving the clinicians the ability to tailor the program and modify it in an ongoing way to meet the needs of the clients. The different levels of disability of the clients enrolled will provide challenges when determining between-group differences.

Strengths of this study include that it collects feasibility data from both clients and clinicians. It is a well-powered study with an active control group to allow comparisons across a range of functional measures. Also, both groups are matched for time in rehabilitation (rather than the intervention as additional therapy) and this will allow direct comparison of the groups.

The novel nature of this bespoke software will provide valuable information to clinicians and researchers looking to improve engagement with rehabilitation, activity within rehabilitation and improved client outcomes in a cost-effective way.

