**Discussion:**

Results from this study will provide a basis for discussion of feasibility of this interactive video technological solution in an inpatient situation. Differences in activity levels between groups will be the primary measure of efficacy. It will also provide data on measures of upper-limb function, balance and mobility.

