#### Sample size and justification

Sample size calculation was based on previously reported clinical trial data and based on the outcome measure of functional reach, that provided baseline mean (standard deviation) data of 25.6 (7.4) cm [14]. Researchers determined that a clinically relevant difference of 3.7 cm would require a sample size of 63 (*P* <0.05, power 80 %). Seventy-four participants will be recruited to allow for a 15 % dropout rate. The proposed size of this study is comparable to more recently published trial data, which suggest that a clinical difference of 3 cm would require 78 participants [3].

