#### Efficacy

##### Physical activity

All participants will have their activity monitored for 1 week during the trial by using an accelerometer (ActivPal; PAL Technologies, Glasgow, UK). These devices have been validated in older people with impaired function [18]. Data will be analysed in each group to determine the amount of time spent in activities of low, moderate and high energy expenditure. Energy expenditure during rehabilitation will also be compared between groups.

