### Data analysis

Data collected during the trial will allow us to describe the participants’ changes in upper-limb function, balance and mobility by using *t* tests or Mann–Whitney *U* tests to compare normally and non-normally distributed data, respectively. Repeated measures analysis of variance will be used to compare changes in the outcome measures over time and between groups (intervention versus control). The level of significance will be set at 0.05.

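### The only sample-size calculation is for functional reach, so the stated 80% power does not apply to the declared primary outcome, activity level

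*Protocol article*

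**What the plan says.** The primary outcome is named twice. The Abstract (Discussion paragraph) says: "Differences in activity levels between groups will be the primary measure of efficacy". The main Discussion repeats it: "The primary outcome of efficacy consists of the differences in activity levels from using video technology in rehabilitation compared with usual rehabilitation".

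The Physical activity section gives the instrument: "All participants will have their activity monitored for 1 week during the trial by using an accelerometer". It then lists several summaries: time at low, moderate and high energy expenditure, and energy expenditure during rehabilitation. None is singled out.

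Sample size and justification works from a different outcome. The calculation was "based on the outcome measure of functional reach", used "baseline mean (standard deviation) data of 25.6 (7.4) cm", and concluded that "a clinically relevant difference of 3.7 cm would require a sample size of 63" at 80% power. It continues: "Seventy-four participants will be recruited to allow for a 15 % dropout rate". Functional reach appears under Standing balance as one of two reach tests, among upper-limb, sitting-balance, step and mobility measures.

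The Discussion also describes the study as well-powered, in a sentence about comparing functional measures between the groups.

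**The concern.** A power statement belongs to one outcome, one effect size and one variance. Here it belongs to functional reach, while the efficacy question is assigned to activity. A reader who takes the 80% figure as a property of the trial will apply it to the primary comparison, where nothing in the document supports it.

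What is at stake is how the activity result is planned for and read. Without a stated detectable difference, nobody can judge beforehand whether the trial can find an activity effect of a worthwhile size. The gap is not something an article would normally leave to a fuller document: the article presents a complete calculation and attaches it to an outcome other than the one it calls primary.

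**Working it through.** **Inputs.** From Sample size and justification: difference 3.7 cm, SD 7.4 cm, power 80%, sample size 63, 15% dropout, 74 recruited. From Data analysis: "The level of significance will be set at 0.05". Assumed, because not stated: two-sided test, 1:1 allocation. For activity, the document gives neither an SD nor a target difference.

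**1. The protocol's own figure.**
- Standardised difference: d = 3.7 / 7.4 = 0.50.
- Normal approximation, per arm: n = 2 × (1.960 + 0.842)² / d² = 2 × 7.85 / 0.25 = 62.8, so 63 per arm and 126 in total. The t-based figure is 64 per arm, 128 in total.
- One-sided 0.05: 50 per arm, 100 in total.
- Dropout: 63 / 0.85 = 74.1, so the 74 recruited follows from treating 63 as the total.

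The figure 63 equals the two-sided requirement per arm. It does not reproduce as a two-group total under either sidedness.

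**2. Power for functional reach with 63 in total.**
- Normal approximation, 31.5 per arm: 0.50 / √(2/31.5) = 0.50 / 0.252 = 1.984; 1.984 − 1.960 = 0.024; power = 51%.
- Two-sample t test, 31 and 32 per arm: 50%.
- All 74 evaluable, t test: 56%.

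**3. What could rescue 80% for functional reach.** An 80%-power t test with 31 and 32 per arm needs d = 0.717. To turn 0.50 into 0.717, the variance must shrink by a factor of (0.50 / 0.717)² = 0.486.
- Baseline-adjusted analysis: 1 − r² = 0.486, so r is about 0.72.
- Change scores: 2(1 − r) = 0.486, so r is about 0.76.

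The protocol states no such correlation.

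**4. What the same numbers mean for activity.** With no activity SD, only SD units are possible (two-sample t test, two-sided 0.05):

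| Evaluable in total | Detectable at 80% power | Power at 0.3 SD | 0.5 SD | 0.6 SD | 0.7 SD |
|---|---|---|---|---|---|
| 63 (31/32) | 0.72 SD | 22% | 50% | 65% | 78% |
| 74 (37/37) | 0.66 SD | 25% | 56% | 72% | 84% |

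If accelerometer loss left 50 usable records (25 per arm, an illustration and not a figure from the document), the detectable difference would be about 0.81 SD.

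**The case against.** Several points can be made for the plan, and most limit how far the criticism reaches.

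- **The trial is not shown to be underpowered for activity.** A reader might infer that from the mismatch. The document gives no expected activity effect or SD, so the inference fails. If the true effect is about 0.7 SD or more, 63 evaluable give roughly 80% power. This stands.
- **The well-powered remark does not claim power for activity.** It is tied to functional measures, the domain in which the calculation was done. This also stands. The remark still fails on its own terms, since the stated inputs give about 50% power for functional reach.
- **A null activity result would not be uninterpretable.** Its estimate and confidence interval can be read without a prior power statement. This stands.
- **Functional reach is not a rival primary outcome.** Both statements of the primary outcome name activity, and none names functional reach. This stands.
- **Sizing on an outcome with published variance is a known practice, and the trial also addresses feasibility and safety.** The protocol does not give this as its reason, and does not say that functional reach stands in for activity. Even if it did, the 80% would remain a statement about functional reach.

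None of these supplies a power statement for the primary comparison.

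**Conclusion.** The point holds in this form: the outcome declared primary is not the outcome used to size the trial, and the stated 80% power therefore does not apply to the primary comparison. With 63 evaluable the trial detects about 0.72 SD in an activity measure at 80% power and has about 50% power at 0.5 SD; with all 74 evaluable the detectable difference is about 0.66 SD. The 80% figure is not supported for functional reach either, where 63 in total gives about 50%.

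These figures assume 1:1 allocation, a two-sided 0.05 two-sample t test, an approximately normal activity measure, and 63 and 74 as totals, which is how the protocol's dropout arithmetic uses them. The functional reach figure further assumes no gain from a pre-post correlation. The textual mismatch itself rests on none of these assumptions. The conclusion concerns what the protocol claims about its sensitivity and does not establish that the sample is too small for activity.

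**What to change.** Keep the sample size and keep activity as primary. Then:

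1. Name one activity measure, from those listed under Physical activity, as the primary variable. Until this is done there is no single SD to work with.
2. Add to Sample size and justification that 63 evaluable in total (1:1, two-sided 0.05, two-sample t test) detects about 0.72 SD in that variable with 80% power, has about 50% power at 0.5 SD, and detects about 0.66 SD if all 74 are evaluable.
3. Convert this to activity units with a blinded pooled SD, but only if enough accelerometer records exist. The protocol says recruitment is under way and gives no count of records.
4. Label functional reach secondary and restate its power as about 50% for 3.7 cm with 63 in total, or state and justify the pre-post correlation that would support a higher figure.
5. Remove or qualify the description of the study as well-powered in the Discussion.

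The cost is a choice of primary variable, a rewritten paragraph and possibly one blinded SD calculation. Recruitment numbers and data collection do not change. The price is that the stated power becomes less favourable.

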### Trial status

Recruitment for this study is still under way.

## Appendix

**Table 1 Tab1:** FIND Study Therapy Delivery Plan

	Control	Intervention
Ward One easily fatigued client	Daily individual therapy Functional based	Daily individual therapy Alternating daily functional based therapy and Jintronix
Ward One standard client	AM Group Therapy	AM Jintronix
	PM Individual as required	PM Individual as required
Ward Two easily fatigued client	AM short AHA session	1 short AHA session
	PM short AHA session	1 short Jintronix
	Weekly PT review	Weekly PT review
Ward Two standard client	Daily AHA session	Daily Jintronix + gait/stairs/bed TF
	1-2x / week PT session	1-2x / week PT session
Ward Two client with higher tolerance	Daily AHA session	Daily Jintronix + gait/stairs/bed TF
	4 days / week seated ex group	4 days / week seated ex group
	1-2x / week PT session	1-2x / week PT session
Ward Two client with high tolerance	Daily AHA session	Daily Jintronix + gait/stairs/bed TF
	4 days / wk functional ex group	4 days / wk functional ex group
	1-2x / week PT session	1-2x / week PT session

PT Physiotherapy, AHA Allied Health Assistant, TF transfers

## Abbreviations

JRS: Jintronix Rehabilitation System
VAS: Visual Analogue Scale
